In the majority of trials reviewed, the method for assessing preferences consisted of administering one item inquiring about participants’ choice, which has three limitations. First, the use of one item, with no demonstrated psychometric properties, could have introduced measurement error, raising questions about the accuracy of the expressed treatment preference in reflecting participants’ choice. Second, the trials’ reports provided minimal details regarding the treatment-related information presented to participants prior to eliciting their preferences, and the format in which such information was given. The content and format for presenting treatment-related information affect participants’ perception of the treatment options [18–20].

Third, single items do not capture the complexity of treatment preferences, which are based on careful evaluation of the treatments’ attributes such as effectiveness, severity of side effects, and convenience of implementing the treatment in daily life [21–23]. Therefore, the method for assessing preferences has to be systematic in order to obtain well-informed and accurate expressions of participants’ preferences.

The two methodological factors were addressed in the current study. The method of allocation to treatment was examined by applying the two-stage partially randomized clinical trial [4] that involved two methods of allocation: random and preference-based. A systematic method, operationalized in the Treatment Acceptability and Preference scale [24], was followed to assess treatment preferences.

The goal of the current study was to clarify the contribution of treatment preferences in intervention evaluation research. The specific study objectives were:To compare participants randomized to treatment and participants allocated to the preferred treatment on: attrition, adherence to treatment, and outcomes.Among randomized participants, to compare those who received matched (i.e. congruent with expressed preferences) and those who received mismatched (i.e. incongruent with expressed preferences) treatment on: attrition, adherence to treatment, and outcomes.

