## Methods

### Design

A two-stage partially randomized clinical or preference trial (PRCT), originally described by Rücker [4], was used. The trial protocol was approved by the Research Ethics Board at Ryerson University (Protocol Reference # 2010-085-3). The research performed on participants were in compliance with the Helsinki Declaration. As illustrated in Fig. 1, the PRCT involves two stages for participants’ allocation to treatment. In the first stage, eligible participants that have provided written informed consent are randomized to the random or preference arms of the trial, after obtaining pretest data. Randomization at this stage increases the likelihood that participants in the two arms are comparable in their socio-demographic and clinical profiles, status on pretest outcomes, and expressed preferences for the treatments under evaluation. In the second stage, the method of assignment to treatment differs between the trial arms. In the random arm, participants are randomly assigned to treatment, whereas in the preference arm, participants are allocated to the preferred treatment. This treatment allocation scheme allows comparisons on relevant variables between participants who receive the same treatment on the basis of either chance or preference; the results of these comparisons determine the contribution of preferences.

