The sample size is estimated to attain adequate power to determine the effects of treatment preferences on attrition, adherence, and sleep outcomes. Sample size estimation also considers the repeated measure feature of the design. Within-subject designs require a smaller number of participants than between-subject designs, to achieve the same statistical power [30]. A medium sized effect (0.5) is anticipated on the basis of: 1) results of a systematic review showing that behavioral therapies had moderate-to-large effects on sleep parameters (sleep onset latency and wake after sleep onset) in middle-aged and older adults [31]; and 2) an expected medium effect for the comparison of participants assigned to treatment randomly or congruent with their preferences. A medium effect is anticipated, rather than a small effect as reported in the literature, with the use of a reliable and valid measure of treatment preferences. Applying Cohen’s [32] criteria for an anticipated medium effect size for the main comparison, the inclusion of four groups (i.e. participants allocated to the stimulus control therapy and those allocated to the sleep restriction therapy either randomly or based on their preference), and setting α at .05 and β at .80, the required sample size is 60 per group, for a total of 240 participants to be recruited.

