*Preferences for treatment* are measured with an adapted version of the Treatment Acceptability and Preference scale [24]. It contains three sections. The first presents the description of one treatment. The description introduces the treatment’s name and goal; explains the activities comprising the treatment, the recommendations to be followed by the participants, the mode of delivery and dose of treatment; and summarizes evidence of the treatment’s benefits and risks. Information on benefits and risks is synthesized from available empirical literature, and presented in simple, non-technical, and easily understood terms. Following the description is a set of items for participants to rate the treatment relative to four attributes: 1) effectiveness in managing insomnia in the short and long term, and in improving daytime functioning; 2) appropriateness or suitability in addressing insomnia; 3) severity of side effects; and 4) convenience, that is, ease of implementing it in daily life. A five-point rating scale, ranging from *not at all* (0) to *very much* (4) is used. The second section of the Treatment Acceptability and Preference (TAP) presents the description of the alternative treatment, and the items for rating it. The third section includes two questions asking participants to indicate if they have a preference for any treatment and, if they do, the preferred treatment. In this study, the nine items rating the attributes of the two behavioral therapies are internally consistent (Cronbach’s alphas > .85) and valid, evidenced by significant associations between the treatments’ ratings and the expressed preferences. The order for presenting the treatment options is randomized to avoid an order effect.

*Attrition* is noted and documented in a log. The research assistants record the following information for each participant: completion of pretest measures, attendance at treatment sessions, completion of post-test, 6-month and 12-month follow-up measures, time at which the participant withdraw and reasons for withdrawal as reported by participants. Attrition rate will be computed as the percentage of participants who drop out of the study at any time after providing consent to take part in the trial.

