### Data analysis

In addition to descriptive statistics to characterize the participants in terms of their demographic and clinical characteristics, the following analyses are planned to address the study objectives:Objective 1: Chi-square test will be used to compare the number of participants who withdrew from the study across the four study groups defined by the type of treatment received (stimulus control therapy and sleep restriction therapy) and the method of allocation to treatment (random and preference). One-way analysis of variance will be applied to examine differences in level of adherence (i.e. attendance to treatment sessions and enactment of treatment recommendations), and the pattern of change (estimated with a slope) in the sleep outcomes, across groups.Objective 2: Chi-square test will compare the number of dropouts between participants in the random arm who receive matched and mismatched treatment. Independent samples t-test will examine differences between the matched and mismatched subgroups in levels of adherence (exposure and enactment) to treatment and the pattern of change in the sleep outcomes.

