Despite its advantages, there are some challenges in carrying out a two-stage PRCT. The first challenge relates to the first stage of randomization. Through the process of obtaining informed consent, participants are informed of the two stages and of the method for treatment allocation within each arm. Participants with strong treatment preferences may be unwilling to leave treatment choice to chance and they may desire allocation to the preference arm. If randomized to the random arm, they may react unfavorably [4] and withdraw from the study.

The second challenge in the implementation of the two-stage PRCT relates to the method of treatment allocation applied in the second stage of the trial. At this stage, participants in the random arm are randomized to treatment, yielding a balanced number of participants assigned to the treatment groups. However, the equality of the treatment groups’ sizes is not achieved in the preference arm if most participants choose one treatment over the other. Large differences in group sizes may yield unequal within-group variances; if not addressed with appropriate statistical formula, unequal variances may reduce the power to detect significant treatment and preference effects [35]. The validity of these conclusions is further jeopardized if the pretest comparability of participants is not maintained. Randomization to treatment, applied in the random arm, increases the likelihood of achieving baseline comparability. However, such comparability may not be observed in the preference arm due to possible differences in the profile of participants choosing the alternative treatments under evaluation. Therefore, the baseline comparability of participants assigned to the different treatments randomly or by preference is not maintained, potentially confounding the results.

The third challenge in conducting the two-stage PRCT relates to the reactions of participants assigned to treatment on the basis of chance or preference. Specifically, participants in the random arm may have preferences for the treatments under investigation. Those randomized to the non-preferred treatment may react unfavorably. In contrast, participants in the preference arm may react favorably because they get the treatment they desire. These reactions may influence the participants’ adherence and responses to the allocated treatment.

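### Attrition is counted from consent but compared across groups defined by treatment received, so as written a withdrawal after randomisation but before treatment falls in no compared group

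*Protocol article*

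**What the plan says.** All references are to the Protocol article.

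- **Attrition window** (Variables and measures): the rate is "the percentage of participants who drop out of the study at any time after providing consent to take part in the trial". The log records when and why each participant withdrew.
- **Order of events** (Design): "eligible participants that have provided written informed consent are randomized to the random or preference arms of the trial, after obtaining pretest data". Treatment is assigned only in the second stage, at random or by preference.
- **Objective 1 test** (Data analysis): a chi-square test compares the number who withdrew "across the four study groups defined by the type of treatment received" and by method of allocation.
- **Objective 2 test** (Data analysis): dropouts are compared "between participants in the random arm who receive matched and mismatched treatment".
- **The objective itself** (Background): "To compare participants randomized to treatment and participants allocated to the preferred treatment on: attrition, adherence to treatment, and outcomes".
- **The same four groups elsewhere** (Sample): "participants allocated to the stimulus control therapy and those allocated to the sleep restriction therapy either randomly or based on their preference".
- **Expected reaction** (Discussion), of participants with strong preferences: "If randomized to the random arm, they may react unfavorably [4] and withdraw from the study".

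**The concern.** The window for counting a withdrawal opens at consent. Membership of a compared group, as the Data analysis section words it, requires that treatment was received. Between those two points lie pretest, randomisation to an arm, and assignment to a therapy. Anyone who leaves in that interval adds to attrition but has no cell in the test.

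Attrition is the first variable named in both objectives, and the trial exists to learn whether ignoring or honouring a preference changes it. A participant who is disappointed by the arm or the therapy can leave before the first session. If such people drop out of the comparison, part of the effect under study is lost from the analysis, and the missing part need not be equal in the two arms.

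The article also uses two group definitions, *allocated* under Sample and *received* under Data analysis. They give different counts whenever someone is assigned a therapy and never starts it.

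**Working it through.** **Step 1. Place each withdrawal on the timeline.** All four types count as attrition under Variables and measures.

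| Time of withdrawal | Arm known? | Group if *received* | Group if *allocated* |
|---|---|---|---|
| (a) consent to stage-1 randomisation | no | none | none |
| (b) stage 1 to treatment assignment | yes | none | none of the four |
| (c) assignment to first session | yes | none | yes |
| (d) after treatment starts | yes | yes | yes |

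Only (d) enters the test on the wording of Data analysis. Reading *received* as *allocated* adds (c). Allocation-triggered losses can fall in (b), (c) or (d). Type (a) cannot be caused by an allocation that has not happened.

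**Step 2. Size, by illustration.** The article states no attrition rate, so there is no figure of its own to reproduce, and the rates below are assumptions. Let w be the share of an arm that leaves between randomisation and treatment, and q the drop-out rate among those who start treatment. Subscripts R and P denote the random and preference arms.

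- Attrition as randomised: w + (1 − w)q
- Attrition by treatment received: q
- If q is the same in both arms, the difference as randomised is (w_R − w_P)(1 − q), and the difference by treatment received is 0.

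Take w_P = 0 and 120 per arm. The 120 follows from the planned 60 per group, with two groups in each arm if sizes are equal.

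| q, both arms | w_R (number of 120) | By treatment received, R v P | As randomised, R v P | Difference lost |
|---|---|---|---|---|
| 10% | 5% (6) | 10% v 10% | 0.05 + 0.95 × 0.10 = 14.5% v 10% | 4.5 points |
| 10% | 10% (12) | 10% v 10% | 0.10 + 0.90 × 0.10 = 19.0% v 10% | 9.0 points |
| 10% | 20% (24) | 10% v 10% | 0.20 + 0.80 × 0.10 = 28.0% v 10% | 18.0 points |
| 20% | 5% (6) | 20% v 20% | 0.05 + 0.95 × 0.20 = 24.0% v 20% | 4.0 points |
| 20% | 10% (12) | 20% v 20% | 0.10 + 0.90 × 0.20 = 28.0% v 20% | 8.0 points |
| 20% | 20% (24) | 20% v 20% | 0.20 + 0.80 × 0.20 = 36.0% v 20% | 16.0 points |

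**Step 3. What the direction depends on.** With q equal, the lost difference has the sign of w_R − w_P. It is zero if early losses are equal. It masks higher attrition in the random arm only if early losses are more common there. The Discussion makes that plausible but gives no rate.

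I give no power figure. A two-arm calculation would not describe the planned test, which is a chi-square across four groups.

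**The case against.** The best reply is that *received* is loose wording for *allocated*. The Sample section describes the same four groups by allocation, and Objective 1 is worded by allocation. No section describes crossover, a per-protocol set, or exclusion of people who never attend, and the exposure measure counts sessions attended, which allows zero. On that reading type (c) withdrawals have a group. This is a fair reading, but the text does not settle it. Two sections define the groups in different words that give different counts, and type (b) still fits none of the four groups.

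Second, losses between consent and stage 1 cannot bias a comparison of arms, because no arm exists yet. That stands. They are a matter for the flow diagram.

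Third, the interval between the two stages may be short. Preferences are collected at pretest, so the therapy of a preference-arm participant who states one could be known as soon as the arm is. The article gives neither the interval nor the moment when participants are told. So type (b) may be small, but it cannot be assumed empty.

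Fourth, such detail can be left to a fuller protocol or analysis plan. That would answer a charge of omission. Here, however, the article itself states the window, the groups and the test, and they do not fit together.

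A reader might also infer that the article presents early withdrawal as a main effect of ignoring preference, or that its analysis breaks both randomisations. Neither is supported. The Discussion calls such withdrawal a challenge that may arise. The randomised comparisons would be compromised only if *received* is meant literally and people who never start are excluded, which no section states.

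**Conclusion.** The point holds as a conflict within the article. The attrition window opens before allocation, while the compared groups are defined, as worded, by a later event. Withdrawals after randomisation and before treatment then have no group, and the random-arm withdrawals that the Discussion foresees may be among them.

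Bias towards no difference is conditional on early losses being more common in the random arm. Its size cannot be computed from the document. Under the assumed rates above, the as-received comparison hides 4 to 18 percentage points. It would be too strong to say that all preference-driven withdrawals are removed, because those that occur after treatment starts are counted on any reading, with the log running to the 12-month follow-up.

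The matter should be settled before analysis, because choosing between the two definitions after seeing the counts would be a post hoc choice on a named study variable.

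**What to change.** 1. For the comparison of arms, count attrition from stage-1 randomisation, with every randomised participant in the denominator of the arm to which they were randomised.
2. For the four-group comparison and for Objective 2, count from treatment assignment, by allocated treatment. Define matched and mismatched by the assigned treatment.
3. Report losses between consent and randomisation separately in the flow diagram, outside the group comparisons.
4. Use *allocated* in both Sample and Data analysis. Apply the same groups to exposure, where a participant who attends nothing scores 0 sessions.

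The cost is a few sentences. The participant log already records the time of and reasons for withdrawal, and follow-up is still being completed, so the rule can be fixed before the analysis without collecting anything new.

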### Data analysis

In addition to descriptive statistics to characterize the participants in terms of their demographic and clinical characteristics, the following analyses are planned to address the study objectives:Objective 1: Chi-square test will be used to compare the number of participants who withdrew from the study across the four study groups defined by the type of treatment received (stimulus control therapy and sleep restriction therapy) and the method of allocation to treatment (random and preference). One-way analysis of variance will be applied to examine differences in level of adherence (i.e. attendance to treatment sessions and enactment of treatment recommendations), and the pattern of change (estimated with a slope) in the sleep outcomes, across groups.Objective 2: Chi-square test will compare the number of dropouts between participants in the random arm who receive matched and mismatched treatment. Independent samples t-test will examine differences between the matched and mismatched subgroups in levels of adherence (exposure and enactment) to treatment and the pattern of change in the sleep outcomes.

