## Discussion

The study is in its final stage of collecting outcome data for the 12-month follow-up. To date, 421 persons showed interest and agreed to undergo initial screening.

The study extends previous research on the role of treatment preferences in intervention evaluation research in two ways. First, the two-stage PRCT design is applied, which is considered the most appropriate design for evaluating the influence of treatment preferences because of its advantages. The PRCT design is useful to dismantle the influence of treatment preferences from the impact of treatment on attrition, adherence and outcomes. This is accomplished by creating groups of participants who receive the same treatment randomly or by preference; comparison of these groups indicates the contribution of treatment preferences to attrition, adherence and outcomes. The PRCT design also minimizes the potential for selection bias resulting from non-comparability of participants assigned to different treatments randomly or on the basis of preference [3, 10]. The advantages stem from the randomization of participants to the random and preference arms in the first stage of assignment. Randomization at this stage maintains a balanced number and comparability on baseline characteristics of participants allocated to the two arms of the trial. This initial comparability reduces the potential for selection bias and confounding of the effects of treatments and preferences. It also enhances the validity of conclusions regarding the effectiveness of the treatments and the influence of preferences on adherence and outcomes of the treatments under investigation.

Second, the study uses a systematic method for assessing treatment preferences. The method begins by providing information on the treatments’ goals, components, activities, mode and dose of delivery, benefits and risks; it proceeds by having participants rate each treatment relative to four attributes prior to indicating their preferences. The TAP measure operationalizes this systematic method, has sound psychometric properties, and is expected to accurately capture participants’ preferences.

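### The four-group test planned for Objective 1 responds to allocation method but is not specific to it, and the same-therapy comparison is read as a preference effect although it is not randomised

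*Protocol article*

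**What the plan says.** The article's Background sets Objective 1 as a two-level question: "To compare participants randomized to treatment and participants allocated to the preferred treatment on: attrition, adherence to treatment, and outcomes".

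Under Data analysis, dropout is compared by chi-square "across the four study groups defined by the type of treatment received" and by the method of allocation. For the remaining variables, "One-way analysis of variance will be applied to examine differences in level of adherence" and in the slopes of the sleep outcomes across the same groups. No single-df test of allocation method is named.

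The Design section and the Discussion explain how results are to be read. Participants who get the same therapy by chance or by preference are set against each other, and the Discussion says that "comparison of these groups indicates the contribution of treatment preferences to attrition, adherence and outcomes". Later the Discussion lists challenges of the design and concludes that "the baseline comparability of participants assigned to the different treatments randomly or by preference is not maintained, potentially confounding the results".

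The Design section adds three relevant facts. Preference is recorded at pretest, before the first-stage randomisation. Preference-arm participants receive the therapy they name. Those with no preference are randomly assigned.

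**The concern.** There are two linked problems.

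1. **The test does not isolate the question.** The null hypothesis of a test over four therapy-by-allocation cells is that all four are equal. A difference between stimulus control and sleep restriction makes that null false even if allocation method has no effect, so a significant result does not by itself answer Objective 1. The two further degrees of freedom also cost some power for the allocation effect.

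2. **The stated reading is not protected by randomisation.** The first stage makes the two whole arms comparable. It does not make the cells within one therapy comparable. The preference-arm cell for a therapy holds people who chose it (plus some with no preference), while the random-arm cell mixes all preferences. If those who prefer one therapy have a different outlook from those who prefer the other, the same-therapy difference contains that gap. The article says both that this comparison shows the contribution of preferences and that it may be confounded.

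At stake is the study's first objective: a therapy difference or self-selection could be reported as an effect of preference.

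**Working it through.** **Inputs from the article (Sample).** "A medium sized effect (0.5) is anticipated"; "setting α at .05 and β at .80", where the second figure is read as power; "the required sample size is 60 per group, for a total of 240 participants to be recruited". Two-sided testing and SD = 1 are assumed.

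**The plan's own figure.** The usual two-mean formula at d = 0.5 and power 0.80 gives 63 per group (64 by t-test). With 60 per group, two-group power is 0.78. A four-group ANOVA at f = 0.25 needs 45 per group for power 0.80. So 60 is not reproduced exactly, but the gap is small on the power scale and has no bearing on this point.

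**Therapy difference only, no allocation effect.** With cell means 0, d, 0, d and n = 60 each, the noncentrality is λ = Σ n(μ − μ̄)² = 240·(d/2)² = 60d². Rejection follows from the noncentral F with 3 and 236 df at α = 0.05.

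| Assumed therapy difference (SD) | λ | Four-group ANOVA rejects |
|---|---|---|
| 0.1 | 0.6 | 9% |
| 0.2 | 2.4 | 22% |
| 0.3 | 5.4 | 47% |
| 0.5 | 15.0 | 91% |

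The chi-square test behaves the same way. If dropout depends on therapy only, at assumed rates of 20% v 30%, λ = 240·0.05²/(0.25·0.75) = 3.2 and the test rejects 29% of the time. At 20% v 40%, λ = 240·0.10²/(0.30·0.70) = 11.4 and it rejects 82%.

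**Power for a pure allocation effect.** With cell means 0, 0, d, d, λ is again 60d², tested with 3 or 1 numerator df.

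| Arm difference (SD) | 3 df | 1 df |
|---|---|---|
| 0.5 (the plan's effect) | 91% | 97% |
| 0.15 | 14% | 21% |

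**Self-selection only, no therapy or allocation effect.** Let a share p prefer therapy A, with a prognosis better by g. Both random-arm cells then have mean pg. The preference-arm cells have means g (A) and 0 (B). The same-therapy differences are (1 − p)g in A and −pg in B.

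- p = 0.7, g = 0.4: 0.3·0.4 = +0.12 and −0.7·0.4 = −0.28 SD. With 84 and 36 in the preference-arm cells, λ = 84·0.12² + 36·0.28² = 4.03, and the omnibus test rejects about 35%.
- The same case with 30% having no preference and average prognosis: the differences shrink to about +0.09 and −0.16 SD, and omnibus rejection falls to about 17% to 19%.
- p = 0.5, g = 0.2: ±0.10 SD, λ = 1.2, rejection about 13%.

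In the first case, the comparison of arms as randomised rejects about 5%, its nominal level.

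**Check on the alternative.** A comparison of arms that leaves therapy out shifts by (share − 0.5)·d when choice is uneven. For a 0.5 SD therapy difference and nothing else, the shift is 0.10 SD at 70/30 and 0.15 SD at 80/20. With 120 per arm, z = shift·√60 = 0.77 and 1.16, so it rejects about 12% and 21%. Adjusting for stated preference alone leaves that shift in place. With therapy also in the model, rejection returns to about 5%.

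**The case against.** - **The test does involve allocation.** Random or preference is one of the two factors that define the cells, and the four-group layout fits the Background's aim of looking within and across therapies. A reader might infer that the omnibus test says nothing about allocation, or that the first-stage randomisation goes unused. The article does not support that. The fault is lack of specificity.
- **No within-therapy contrast is planned in so many words.** Data analysis names none, and follow-up contrasts or covariates may stand in a fuller document. This stands, so the absence of adjustment is not counted here. The same-therapy reading comes from the Design section and the Discussion, and it is the interpretation stated there that conflicts with the later concession.
- **The confounding is disclosed.** True. What remains is that the Discussion asserts one reading and later undercuts it.
- **The sizes rest on assumptions.** Also true. The article gives no gap between the therapies, both active and given in the same dose and format. It gives no choice shares and no prognostic gap either. For sleep outcomes, which are analysed as slopes, a stable difference in level cancels, so the gap would have to be in rate of change. That does not help attrition or adherence.
- **The power loss is modest at the plan's own effect.** A reader might take the literature value of 0.31 as an arm difference and infer a larger loss. The Background describes that value as preferred v randomised to non-preferred treatment. The random arm mixes matched and mismatched participants, so if half are matched the arm difference is about 0.31/2 = 0.155. Power is then low with either test.

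**Conclusion.** The point holds in this form: the stated Objective 1 test is sensitive to allocation method but not specific to it, and the interpretive text conflicts with the article's own caveat. The first part needs no assumption about selection, and its size depends only on how far the therapies differ (9% to 91% rejection over 0.1 to 0.5 SD with no allocation effect). The second part is certain in direction of reasoning but not in size. The cases worked here run from about 13% to 35% omnibus rejection, and the figure would be smaller still with a smaller gap.

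This should be fixed, but it does not undermine the design. Separating the two factors is compatible with the four groups as planned, and the randomised comparison that Objective 1 needs is available in the data.

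**What to change.** 1. Make the main Objective 1 test a 1-df test of first-stage arm as randomised, from a linear model (logistic for attrition) that includes stated pretest preference in three levels: each therapy, or none.
2. Report it in two versions: without therapy, as the total effect of offering choice, and adjusted for therapy allocated. State that the version without therapy also moves with therapy mix when choice is uneven.
3. As a secondary analysis, compare choice with chance among participants with the same stated preference who got the same therapy, leaving out those with no preference.
4. Keep the four-group chi-square and ANOVA as descriptive.
5. Reword the Design and Discussion statements on the same-therapy comparison to agree with the Discussion's caveat on comparability.

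The cost is analysis and wording only. Preference is already recorded in everyone before the first stage, and the article says 12-month outcome data were still being collected. The one downside is that the secondary contrast uses only about half of the random arm, since about half are randomised to the therapy they prefer.
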